**Fig. 2 Fig2:**
[figure not shown]
Interactive systems framework and stages of the implementation study

#### Aim 1

Refine strategies I (training) and II (TIER) using semi-structured interviews with stakeholders—parent advocates, multidisciplinary health care providers, national pediatric oncology professional organizations, and health care industry leaders (implementation team).

#### Aim 2

Compare the two theoretically based and empirically informed strategies to implement the PAT in English and Spanish using a cluster-randomized controlled trial. Compared to training:

**H2.1**. At the patient/family level, TIER will be associated with: (a) a higher proportion of families of newly diagnosed children screened and provided with feedback (penetration) and (b) higher rates of screening for ethnic minority and socioeconomically diverse families (health equity).

**H2.2**. At the provider level, TIER will be (a) more feasible and rated as appropriate and acceptable, (b) associated with greater engagement in addressing health disparities, and (c) associated with less burnout and better job satisfaction.

**H2.3**. At the institution level, TIER will be associated with: (a) a higher rate of site participation (adoption), (b) more positive perceptions of implementation benefits and fewer challenges (sustainability), and (c) psychosocial care better matched to need demonstrating a more equitable distribution of services and costs of care.

#### Aim 3

Based on the results of the trial and further guidance from the implementation team, we will integrate acceptable, feasible, and effective strategies to develop and disseminate a web-based PAT Implementation Toolkit.

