#### Measurement/outcomes (all sites)

The measures assess outcomes across patient/family, provider, and institution levels (Table 1) that are clearly operationalized and reproducible [46]. Site PIs and coordinators will attend training on data collection procedures, in separate sessions for the two conditions.

**Table 1 Tab1:** Measurement

Level/Hyp	Concept	Source	Metric/measure
Patient/family 2.1	Penetration Health equity	EHR (monthly)	Demographics: race, ethnicity, zip code, insurance No. eligible families, English/Spanish No. eligible families screened, English/Spanish % Family feedback letter provided
Provider 2.2	Feasibility Appropriateness Acceptability Engagement in addressing health disparities Job satisfaction Burnout	Survey (Pre, 6-month, Post)	Acceptability of intervention measure Intervention appropriateness measure Feasibility of intervention measure AREA scale of physician engagement Satisfaction employees healthcare Maslach Burnout Inventory version for Medical Personnel
Institution 2.3	Adoption Sustainability: perceived benefit Cost-effectiveness: services/need and cost	Survey	Site participation rate PAT implementation questionnaire
		EHR (monthly)	Psychosocial Services and Medical Treatment Checklist Intensity of Treatment Rating Scale

At the patient/family level (Hyp 2.1) the site coordinator will extract EHR data and send the coded data via REDCap to the data core. The following data for English and Spanish versions of the PAT will be reported monthly: new patients meeting eligibility requirements per the PAT implementation plan; patients with documentation of PAT screening; patients receiving feedback letter; demographic data on all eligible and all screened (race, ethnicity, zip code, insurance).

At the provider level (Hyp 2.2), the site PI and screeners will complete the following self-report measures (~ 15 min) at baseline (T1), and 6 (T2) and 12 (T3) months via REDCap: acceptability of intervention measure; intervention appropriateness measure and feasibility of intervention measure [47]; measure of physician engagement in addressing racial and ethnic health care disparities [48], satisfaction of employees in healthcare survey [49], and Maslach Burnout Inventory [50].

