PAT implementation will be tested using a head-to-head randomized implementation (comparative effectiveness of two implementation strategies) trial in three cohorts over 3 years. *Randomization*. Eighteen sites will be randomized to one of three cohorts. Each cohort will be further randomized to one of the two strategy conditions. Randomization will stratify sites by size to maximize internal validity and statistical power. Sites will be randomized by a data analyst not connected with the study using a two-step Excel = RAND() function. The sequence will be stored in a password-protected electronic file. *Sample size*. The estimated sample of patients/families is based on the median number of new patients each year from the PIPS-CSS database: small (*n* = 60), medium (*n* = 92), large (*n* = 339) multiplied by 6 sites at each size, a total of 2946, with 1473 families allocated to each strategy. With an anticipated Interclass Correlation Coefficient (ICC) [65] of .005, the effective sample size is 950 per arm, a sample size that is sufficient to detect a small effect between the two strategies given 80% power (alpha = .05, one sided). We project a Hispanic sample of 20% of the total (*n* = 589). Based on our research [8], approximately 30% of Hispanic caregivers will be more acculturated/not literate in Spanish at the level necessary to complete the Spanish PAT, rendering a sample of 412. With an anticipated ICC of .005, the effective sample size is 224 which is sufficient to detect a medium effective between the English and Spanish versions given 80% power (alpha = .05, one sided). At the provider level, each of 18 sites has a PI and up to four people screening, and for TIER sites, a champion. Therefore the staff sample ranges from a minimum of 45 ([18 × 2] + 9) to a maximum of 99 ([18 × 5] + 9), likely in the middle given the range of size of sites. At the institution level, 18 sites will be randomly assigned to one of two strategies (9 sites/group). These sample sizes are comparable to other implementation science studies [66].

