#### Data cleaning and missing data

All data will be reviewed for valid values/data entry errors, outliers, and extent/pattern of missing data. Descriptive statistics will be reviewed. Consistency and logic checks will be applied for review/cleaning. The multiple group analysis models will provide valid estimates of efficacy if the proportion of missing values is < 10%. Analysis will be conducted at the patient/family, provider, and institution levels. The effect of program size and cohort will be examined and controlled if needed.

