H2.1. ANOVA will compare the effectiveness of the two implementation strategies on penetration and health equity. The outcomes are proportions: families screened/families eligible, families provided feedback/families screened, ethnic minority families screened/ethnic minority families eligible, low SES families screened/low SES families eligible. ICCs among the clusters will be calculated and used to adjust for the cluster effect [67, 68].H2.2. Three sets of outcome variables—perception of implementation, engagement in addressing health disparities, and burnout/job satisfaction—will be tested. A two group analysis using Structural Equation Modeling (SEM) will compare the effectiveness of the two strategies [69, 70]. To test the effect of time, we will conduct latent growth curve analysis [71–73]. Analyses will be conducted using Mplus 5.0 [74] with ML estimation for outcome variables that meet the distribution assumptions, and WLSMV estimation for variables that do not. Potential mediating effects of favorable perception of implementation on provider job satisfaction and burnout will be examined using mediation models. TIER is expected to be associated with more favorable perceptions of implementation, less burnout, and higher job satisfaction.H2.3. At the institution level, adoption of the PAT will be measured by a ratio of sites that initiate implementation/sites that agreed (H2.3a). If substitutions are necessary, sites that are newly invited will be added to the denominator and adoption calculated by total acceptances/total invited. ANOVA will be conducted to compare the effectiveness of the two strategies. For H2.3b sustainability (PIQ perceptions of implementation benefits and challenges), ANOVA will be conducted to compare the effectiveness of the two strategies on benefits and challenges. For H2.3c, we are interested in the extent to which psychosocial care is matched to need. A cost-effectiveness threshold or criterion to which to compare costs of screening with these two implementation strategies has not been established, necessitating our consideration of valued outcomes in the psychosocial screening literature and resources available. We will use a data analytic approach that we used previously [18]. ANOVA will be conducted to test whether psychosocial care is matched with levels of psychosocial risks, resulting in a 2 (strategy) × 3 (psychosocial risks: clinical, targeted, universal) design on equitable distribution of services and costs of care. It is expected that the 3 PPPHM levels will be related to number and costs of services provided as measured on the PSMTC, with least at universal and most at clinical. It is expected that TIER will result in a better match between level of risk and services provided. Scores from the PSMTC will be derived and mapped onto the levels of the PPPHM. Additional analyses will be conducted to compare English speaking and Spanish speaking families, different ethnicity, race, and SES and insurance status on the outcome variables for H2.3c.

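### H2.2: the strategy comparison does not bring in the T1 scores, and the growth curve is aimed at time rather than at the strategy difference in change

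*Protocol article*

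**What the plan says.** The hypothesis is comparative. Under Specific aims, Aim 2, H2.2, TIER relative to Training is expected, among other things, to be "associated with less burnout and better job satisfaction".

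Measurement/outcomes (all sites) has the site PI and screeners complete the H2.2 scales "at baseline (T1), and 6 (T2) and 12 (T3) months via REDCap". Baseline scores on every H2.2 outcome will therefore exist.

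The H2.2 paragraph of the Aim 2 data analysis names three outcome sets, "perception of implementation, engagement in addressing health disparities, and burnout/job satisfaction", and gives two models separate purposes:
- strategy: "A two group analysis using Structural Equation Modeling (SEM) will compare the effectiveness of the two strategies";
- time: "To test the effect of time, we will conduct latent growth curve analysis".

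On covariates, the Data cleaning and missing data section says only: "The effect of program size and cohort will be examined and controlled if needed". The T1 score is not named there or in the H2.2 paragraph.

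**The concern.** H2.2 needs a between-strategy contrast that uses the repeated measurements well. There are two natural candidates: the strategy difference at 12 months given the same person's T1 score, or the strategy difference in change over time. The article states neither. Its strategy model has no stated wave and no stated role for T1. Its longitudinal model has a stated target, and that target is not the H2.2 question: staff in both arms may change equally over a year, which gives a clear time effect and no information about TIER.

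Two things are at stake. The first is precision at a level of the trial where the respondents are few and sit in 18 randomized sites. The second is interpretation: once results are known, it should already be settled which contrast decides H2.2.

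**Working it through.** **Inputs from the protocol article**
- Staff sample (Data analysis, Aim 2, sample size): 18 × 2 + 9 = 45 to 18 × 5 + 9 = 99. Both figures reproduce exactly.
- The 9 are the TIER champions. Measurement/outcomes lists only the site PI and screeners for the H2.2 scales, so the H2.2 respondents number 45 − 9 = 36 to 99 − 9 = 90.
- Nine sites per strategy, two to five respondents per site, so 18 to 45 respondents per arm.
- No provider-level power, alpha or detectable effect is given, so there is no figure of the plan's to correct.

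**Assumptions (not in the article)**
- Correlation r between T1 and 12 months on the same scale: 0.3 to 0.7.
- Equal variances at the two times, in standard deviation (SD) units.
- Where clustering is shown, an intraclass correlation of 0.05 among staff of a site.

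**Step 1. Precision of three contrasts.** Relative to a 12-month comparison without T1 (variance 1), adjustment for T1 has variance 1 − r². A T1-to-12-month change has variance 2(1 − r). A linear slope over 0, 6 and 12 months has the same relative variance as that change when the three waves are equally correlated.

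| r | 1 − r² | SE, T1-adjusted | Reduction in SE | 2(1 − r) | SE, change or slope |
|---|---|---|---|---|---|
| 0.3 | 0.91 | 0.954 | 5% | 1.40 | 1.183 |
| 0.5 | 0.75 | 0.866 | 13% | 1.00 | 1.000 |
| 0.7 | 0.51 | 0.714 | 29% | 0.60 | 0.775 |

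T1 adjustment gains at every r. The change or slope contrast loses precision at r = 0.3, breaks even at 0.5 and gains at 0.7. Both address the strategy question under randomization, but they are not interchangeable in precision.

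**Step 2. Standard error of the unadjusted difference.** Without clustering it is √(2/n per arm): √(2/18) = 0.33 SD and √(2/45) = 0.21 SD. With an intraclass correlation of 0.05, the design effect is 1 + (2 − 1) × 0.05 = 1.05 or 1 + (5 − 1) × 0.05 = 1.20, giving √(2 × 1.05/18) = 0.34 and √(2 × 1.20/45) = 0.23.

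**Step 3. Detectable difference.** This uses 80% power, 16 degrees of freedom for 18 sites, and the one-sided 0.05 that the article states for the family level, borrowed here. The multiplier is t(0.95, 16) + t(0.80, 16) = 1.746 + 0.865 = 2.611.
- 36 respondents: 2.611 × 0.342 = 0.89 SD unadjusted; × 0.954, 0.866, 0.714 = 0.85, 0.77, 0.64 with T1.
- 90 respondents: 2.611 × 0.231 = 0.60 SD unadjusted; 0.58, 0.52, 0.43 with T1.

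**Step 4. Effect of a chance T1 gap.** Given a gap of 0.25 SD between arms at T1, an unadjusted 12-month difference is shifted by r × 0.25 = 0.08, 0.13 or 0.18 SD for r = 0.3, 0.5 or 0.7. This shift averages to zero over randomizations and is already part of the standard error in Step 2, so it is the Step 1 loss seen from another side and not an additional harm.

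**The case against.** The strongest reply is that the article is silent on T1 and does not exclude it. A two-group structural equation model can carry T1 as a covariate or as a predictor of later waves. A growth curve over three waves uses T1 to define the intercept and, if fitted by group, gives the strategy difference in slope. The missing-data paragraph speaks of multiple-group models in the plural when it refers to efficacy estimates, which is compatible with a multi-group growth model. Covariate lists also commonly sit in a statistical analysis plan, which is not shown here.

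Most of this stands, and it rules out stronger readings. A reader might infer that the H2.2 comparison will certainly be unadjusted; no sentence says so. A reader might infer that chance T1 differences bias the result; under randomization they do not, and the cost is precision. A reader might also expect a time effect to be presented as support for TIER; H2.2 and the closing expectation in its analysis paragraph are both framed as a comparison, so the article does not indicate that.

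The reply does not remove the point. The article is specific here: it names the models, the software version, the estimators and the mediation analysis, and it says what each model is for. The purpose it gives the longitudinal model is the non-comparative one. That is a stated target that does not match the hypothesis, and so is more than a detail left out for length.

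**Conclusion.** The point holds as a low-cost improvement to a stated analysis, not as an error that invalidates H2.2. As written, no named test is the T1-adjusted strategy difference or the strategy difference in change, although the data for both will be collected. Should the comparison be run without T1, it would remain valid but have a larger standard error than necessary: adjustment would lower it by about 5%, 13% or 29% at correlations of 0.3, 0.5 or 0.7. These correlations are assumptions; the article gives no figure for the stability of any H2.2 scale, and at the low end the gain is small. The detectable differences also rest on the assumed intraclass correlation, equal arms and the borrowed one-sided alpha. That a time effect alone does not test TIER against Training rests on none of these assumptions.

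**What to change.** In the H2.2 analysis paragraph, state that the test of H2.2 is the TIER-minus-Training difference at 12 months, adjusted for the same scale at T1, for example with T1 as a covariate in the two-group structural equation model. Add that, where growth curves are fitted, the contrast of interest is the strategy difference in slope and not the time effect. Because the slope contrast can be less precise than the T1-adjusted one (Step 1), the text should keep the two distinct.

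The cost is one or two sentences and no new data. If a statistical analysis plan already says this, the article's wording only needs to be read alongside it.

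### H2.2 selects WLSMV by distributional shape; on skewed continuous scale scores this gives up likelihood handling of missing waves and can bias the growth curve

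*Protocol article*

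**What the plan says.** The rule is in the protocol article, Data analysis, Aim 2, in the H2.2 text under the heading Data cleaning and missing data. The outcomes are named first: "Three sets of outcome variables—perception of implementation, engagement in addressing health disparities, and burnout/job satisfaction—will be tested". The between-strategy analysis follows: "A two group analysis using Structural Equation Modeling (SEM) will compare the effectiveness of the two strategies". Change over time has its own model: "To test the effect of time, we will conduct latent growth curve analysis". The estimator is then chosen by outcome: "with ML estimation for outcome variables that meet the distribution assumptions, and WLSMV estimation for variables that do not". The Abbreviations list expands WLSMV as a robust form of weighted least squares and does not mention categorical data.

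Under Measurement/outcomes (all sites), the provider scales are collected "at baseline (T1), and 6 (T2) and 12 (T3) months via REDCap", so each person contributes up to three waves.

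On missing data the article says "The multiple group analysis models will provide valid estimates of efficacy if the proportion of missing values is < 10" per cent. It names no missingness mechanism and gives no expected drop-out rate for staff.

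**The concern.** The switch to WLSMV depends on the shape of the distribution, not on the measurement level. WLSMV is a limited-information estimator built for ordered-categorical variables through thresholds and polychoric correlations. Skewness in a continuous score, which burnout or satisfaction totals may well show, is not a reason to choose it. The usual remedy is maximum likelihood with robust standard errors, which leaves the point estimation and the use of incomplete records unchanged.

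The choice matters because of missing waves. Full-information likelihood uses every wave a person supplied and remains valid when a missing 6- or 12-month form depends on that person's earlier observed scores. WLSMV works from pairwise-available data and is not valid in general under that mechanism when the earlier scores are themselves outcomes, as they are in a growth curve. Following the rule as written, one H2.2 scale could be analysed under the weaker assumption and the next under the stronger one, with the choice made after looking at the data.

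The estimated time trend is at stake first. The strategy comparison is at stake if drop-out works differently in the two arms.

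**Working it through.** **The plan's own figure.** The article states that "the staff sample ranges from a minimum of 45 ([18 × 2] + 9) to a maximum of 99 ([18 × 5] + 9"). This reproduces: 18 × 2 + 9 = 45 and 18 × 5 + 9 = 99. With 9 sites per strategy, the training arm has 9 × 2 = 18 to 9 × 5 = 45 staff. TIER, with one champion per site, has 18 + 9 = 27 to 45 + 9 = 54. No effect size, power or drop-out rate is given for H2.2, so nothing else there can be reproduced.

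**Assumptions not in the documents.**
- Three waves, SD = 1, between-wave correlation 0.5 or 0.7.
- 12-month loss of 10, 20 or 30%. Its probability follows a logistic model in 6-month burnout with slope 1 per SD.
- TIER lowers burnout by 0.3 SD at 6 months and 0.5 SD at 12 months.
- Either both arms share the mechanism, or burnout drives loss in the training arm only and TIER loses the same share at random.
- A variant uses gamma-skewed scores.

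**Method.** Large-sample simulation, 1,000,000 per arm. Two estimates of the 12-month mean are compared:
- Pairwise: the mean of the observed 12-month scores, which is what a pairwise-present estimator uses without covariates.
- Likelihood: 12-month score regressed on the two earlier waves among those observed, with predictions averaged over everyone.

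**Bias of the pairwise estimate, in SD.** The difference is TIER minus training, so a positive bias pulls TIER's assumed benefit towards no effect.

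| Correlation | Loss | Training-arm 12-month mean | Difference, shared mechanism | Difference, training arm only |
|---|---|---|---|---|
| 0.5 | 10% | -0.046 | 0.009 | 0.046 |
| 0.5 | 20% | -0.087 | 0.018 | 0.087 |
| 0.5 | 30% | -0.125 | 0.020 | 0.125 |
| 0.7 | 10% | -0.063 | 0.012 | 0.066 |
| 0.7 | 20% | -0.121 | 0.021 | 0.122 |
| 0.7 | 30% | -0.180 | 0.030 | 0.176 |
| 0.7, skewed | 10% | -0.097 | not run | 0.096 |
| 0.7, skewed | 20% | -0.148 | 0.017 | 0.149 |

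With no true strategy effect and a shared mechanism, the bias in the difference is zero within simulation error (at most 0.003). The likelihood estimate of the difference is within ±0.003 of the truth in every scenario, including the skewed ones.

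**From the mean to the growth curve.** For a straight line fitted with equal weights to three equally spaced means, the slope per wave is (mean at T3 − mean at T1)/2. The fitted change over 12 months is twice that, T3 − T1, so a bias in the T3 mean passes in full into the estimated change. Other weights would alter the share.

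**Against sampling error.** Ignoring clustering and loss, the standard error of a two-arm mean difference is √(1/18 + 1/27) = 0.30 SD at the smallest sample and √(1/45 + 1/54) = 0.20 SD at the largest. At 20% loss, the shared-mechanism bias is 0.018/0.30 = 0.06 to 0.021/0.20 = 0.11 of a standard error. The one-arm bias is 0.087/0.30 = 0.29 to 0.122/0.20 = 0.61.

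**The 10% statement.** At the edge of that limit, an arm's mean is still off by 0.05 to 0.06 SD (0.10 if skewed). Validity depends on the mechanism as well as on the proportion missing.

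**The case against.** The strongest reply is that the article speaks only of outcome variables in an SEM. If Likert items enter as ordinal indicators, WLSMV is a standard choice, and variables failing the distribution assumptions can be read as exactly those items. This stands, and it limits the point to continuous scale scores. It does not remove the point, because the written trigger is distributional shape and nothing confines WLSMV to categorical indicators.

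Second, an article may leave covariates and missing-wave handling to a fuller document. That is fair for the details. The estimator rule, however, is stated here. If baseline were conditioned on as a covariate, loss driven by baseline alone would be dealt with; loss driven by the 6-month score would not.

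Third, nothing in the article says that burnt-out staff drop out. This stands: the mechanism is a hypothesis. TIER's monthly calls and champion make different drop-out by arm conceivable, but it is not documented.

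Fourth, the size. A reader might infer that H2.2's strategy comparison is biased outright, by 0.12 SD at 10% loss and 0.21 SD at 20%. Those figures follow from 0.6 × φ(z)/(1 − q): 0.6 × 0.195 = 0.117 and 0.6 × 0.350 = 0.210. They require everyone above a baseline burnout cut-off, and no one else, to leave, and in one arm only. The documents support no such pattern.

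A reader might also infer that WLSMV forces scores to be cut into categories, or puts effects on a probit scale. It can be run on continuous scores, and the probit scale arises only for categorised outcomes.

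Finally, the small-sample behaviour of robust maximum likelihood with so few staff has not been shown here.

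**Conclusion.** The point holds in a limited form. As written, the rule sends any non-normal H2.2 outcome to an estimator meant for ordered-categorical data. For a skewed continuous scale score this weakens the handling of missing waves without need, and the missing-data assumption becomes dependent on a distribution check. The 10% statement does not repair this.

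Under the assumed burnout-dependent loss, the growth curve is the part most clearly exposed, by roughly 0.05 to 0.12 SD in an arm's 12-month mean at 10 to 20% loss and about 0.15 SD if scores are skewed. The strategy contrast is barely affected (0.01 to 0.02 SD) unless the mechanism differs by arm, when the bias is 0.05 to 0.12 SD, or up to 0.15 SD if skewed. These sizes rest on assumed correlations and drop-out. The defect in the rule does not depend on them, but it does depend on the outcomes being scale scores, which the article leaves open.

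**What to change.** Replace the estimator sentence in the H2.2 text with:

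*Scale scores will be analysed with robust full-information maximum likelihood (MLR) over T1-T3 whatever their distribution. WLSMV will be used only for outcomes or indicators modelled as ordered-categorical, including multi-item ordinal factors, with its missing-data assumption stated.*

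State for each H2.2 measure whether it enters as items or as a score. The cost is one sentence and that short list. The named software offers the option, and no data collection changes. It should be settled before the outcome distributions are examined.

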### Cluster-randomized comparative effectiveness trial (aim 2)

PAT implementation will be tested using a head-to-head randomized implementation (comparative effectiveness of two implementation strategies) trial initiated in three cohorts of 1 year each (2021, 2022, 2023). All 18 pediatric cancer programs invited to participate in the trial agreed to a 2-step randomization process stratified by size of site; sites will be randomized to one of three cohorts and then to strategy, comparing strategy I (training) with strategy II (TIER).

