The outcomes at the institution level (Hyp 2.3) are as follows: adoption, the intention of sites to use the PAT (the ratio of sites that initiate the study); whether screening is perceived as an asset to the institution using the PAT Implementation Questionnaire (PIQ) [35] which will be completed by the site PI, the screeners, and the champion at T1, T2, and T3; whether services are matched to the needs of families based on PPPHM levels using EHR data using the Psychosocial Services and Medical Treatment Checklist (PSMTC) [18] at 30, 60, and 90 days; cost using the data from the PSMTC to estimate the amount of psychosocial staff time and national median hourly salary data [51–53]. The Intensity of Treatment Rating Scale (ITR-3) [54] will be completed at the 90-day post-screening data collection time point based on diagnosis, stage, and treatment.

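### H2.3a tests adoption, a yes/no outcome on 18 sites, by ANOVA, which is undefined if every site starts and poorly suited when nearly all do

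*Protocol article*

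**What the plan says.** The hypotheses under Aim 2 (Specific aims) predict, in H2.3(a), that sites assigned to TIER will adopt the PAT at a higher rate than sites assigned to training alone. The H2.3 paragraph of the data analysis section defines the outcome: "adoption of the PAT will be measured by a ratio of sites that initiate implementation/sites that agreed". If sites have to be replaced, the definition changes, and the test follows directly: "adoption calculated by total acceptances/total invited. ANOVA will be conducted to compare the effectiveness of the two strategies". H2.3b comes next with its own ANOVA, so this one belongs to adoption.

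The sample size text under Aim 2 puts nine sites in each strategy. It states no alpha, power or expected start rate at the institution level. The opening of the section on the cluster-randomized trial reports that "All 18 pediatric cancer programs invited to participate in the trial agreed" to the randomisation. The Discussion allows for sites becoming unavailable and says that other eligible sites could be approached.

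**The concern.** Adoption is binary at the level of the site, and the site is the unit of randomisation. ANOVA compares means using a variance estimated within arms and assumed equal across them. With 0/1 data the variance is fixed by the proportion and falls to zero as the proportion reaches 100%. Adoption can be expected to lie towards that end, because the event counted is only that a site which has already agreed goes on to start.

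If every site starts, the named analysis gives no p-value and no usable measure of uncertainty, and the text names no other method. A result of 100% v 100% would then stand without any statement of how large a difference nine sites per arm could have missed.

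**Working it through.** **Inputs.** 18 sites, two strategies (Aim 2, sample size). Yes/no outcome per site and ANOVA (H2.3 paragraph). All 18 sites agreed (trial section). The start rate is not given, so it is assumed and varied below.

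**The plan's own figure.** 18 / 2 = 9 sites per strategy. This reproduces.

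**Reading 1: one ratio per arm.** Two numbers in two groups leave 2 - 2 = 0 residual degrees of freedom. No F test exists, whatever the data.

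**Reading 2: 0/1 per site, 16 residual degrees of freedom.**

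*All sites start (9/9 v 9/9).* The between-arm and within-arm sums of squares are both 0, so F = 0/0. Running the test in software returns no value. The pooled standard error is 0. For comparison:
- Wilson 95% lower limit for 9/9 = 9 / (9 + 1.96²) = 9 / 12.84 = 70.1%
- Newcombe 95% interval for the difference = 0 ± (100 - 70.1) = about -30 to +30 points
- Fisher exact p = 1.00

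*One site does not start (9/9 v 8/9).*
- Sample variances in the arms: 0 and (8/9 × 1/9) × 9/8 = 0.111
- Pooled variance = (0 + 0.111) / 2 = 0.0556
- SE = √(0.0556 × 2/9) = 0.111
- Difference = 0.111, so F = 1.0 and p = 0.33
- ANOVA 95% interval = 0.111 ± 2.12 × 0.111 = -12 to +35 points
- Newcombe 95% interval = -20 to +44 points

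The test can be computed here, but one arm has no variance at all and the interval is narrower than the score-based one.

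**How often the boundary is met.** P(all 18 start) = p^18. P(at least one arm at 9/9) = 1 - (1 - p^9)².

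| Assumed start rate per site | All 18 start | At least one arm at 9/9 |
|---|---|---|
| 90% | 15% | 62% |
| 95% | 40% | 86% |
| 98% | 70% | not needed |

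All 18 starting becomes more likely than not only when p is at least 0.5^(1/18) = 96.2%.

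**Type I error.** All 10 × 10 outcomes for 9 v 9 were enumerated with the two-sided 5% F test. Its size is 4.8% at a common start rate of 75%, 3.5% at 80%, 0.7% at 90% and 0.08% at 95%. The maximum over all rates is 5.7%.

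**The case against.** The strongest reply is that little turns on the choice of test. If all 18 sites start, an exact test gives p = 1 and is no more informative about strategy. Away from that case the F test holds its level or is conservative. The real limit is nine sites per arm, which no method removes. This stands as an argument for calling the point minor. It does not rescue a named analysis that cannot be computed in a plausible outcome.

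Three stronger readings are tempting, and the document does not support them.
- **That all 18 starting is the likely result.** No start rate is given. Agreement came before sites knew their strategy or cohort, and substitutions are foreseen. The only site-level rate in the text is the pilot's 9 of 12 centers (75%), which would give 0.75^18 = 0.6%. That rate is for successful implementation, a stricter event than starting, so it does not settle the matter either.
- **That the test also breaks down close to the boundary.** It does not. Because the variance is pooled, one arm at 9/9 is not enough: 9/9 v 8/9 has a standard error of 0.111.
- **That the plan would publish a zero-width interval.** It promises an ANOVA and states no confidence interval for adoption. The zero standard error is a property of the method, not a result that the plan says it will report.

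It may also be said that reporting a degenerate result is detail for an analysis plan not shown here. That would hold if the method had been left open. The article names ANOVA, and an analysis plan that follows it inherits the problem.

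**Conclusion.** The point holds in limited form. ANOVA is unsuitable for H2.3a: it never gives a test on one ratio per arm, and on site-level values it gives none when all 18 sites start. That outcome has a probability of 15% to 70% over assumed start rates of 90% to 98%. Near the boundary the test works but rests on an equal-variance assumption that fails, and its interval differs by about 8 to 9 points at each end from the score-based one for 9/9 v 8/9. There is no material inflation of type I error.

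The figures assume sites that start independently at a common rate and, for the Newcombe intervals, arms treated as independent samples of nine. They ignore the stratification by size and cohort. The consequence is confined to one of several institution-level outcomes, for which the article claims no power.

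**What to change.** Replace ANOVA for H2.3a by the number of sites that start over the number of sites in each randomised arm. That denominator is nine without substitutions; with substitutions, give the per-arm denominator actually used. Add the risk difference with a 95% interval from a score or exact unconditional method. If a p-value is wanted, use an exact unconditional test, or a permutation test that follows the stratified randomisation.

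State in advance that if every site starts, the report will say that no difference was seen but that differences of up to about 30 points are not excluded (nine v nine sites, arms treated as independent).

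The cost is a sentence or two in the analysis text and no new data. The downside is that the stated result becomes less definite.
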